## Abstract

**Background:**

Following stroke, many people have difficulty activating their paretic muscles quickly and with sufficient power to regain their balance by taking quick and effective steps. Reduced dynamic balance and mobility following stroke, or ‘walking balance’, is associated with reduced self-efficacy and restrictions in daily living activities, community integration, and quality of life. Targeted training of movement speeds required to effectively regain balance has been largely overlooked in post-stroke rehabilitation. The Fast muscle Activation and Stepping Training (FAST) program incorporates fast functional movements known to produce bursts of muscle activation essential for stepping and regaining standing balance effectively. The purpose of this study is to: 1) compare the effectiveness of an outpatient FAST program to an active control outpatient physiotherapy intervention in improving walking balance following stroke, and 2) explore potential mechanisms associated with improvements in walking balance.

**Methods/Design:**

This will be an assessor-blinded, parallel group randomized controlled trial design. Sixty participants (30 per group) who have sustained a stroke within the previous six months will be randomly assigned with stratification for lower limb motor recovery to receive twelve 45-minute 1:1 physiotherapy intervention sessions over 6 – 10 weeks in an outpatient setting of either: 1) FAST intervention - systematic and progressive practice of fast squatting and stepping exercises, or 2) active control - conventional physiotherapy directed at improving balance and mobility that includes no targeted fast movement training. The same blinded research physiotherapist will assess outcomes at three time points: 1) baseline (prior to intervention), 2) follow up (within one week post-intervention); and 3) retention (one month post-intervention). The primary outcome is dynamic balance assessed using the Community Balance and Mobility Scale. We will also assess fast and self-selected walking speed, balance self-efficacy, and the ability to respond to internal and external perturbations to balance and associated changes in postural muscle activation.

**Discussion:**

The targeted training of fast functional movements in the FAST program is expected to improve walking balance following stroke compared to the active control intervention. Unique to this study is the investigation of potential mechanisms associated with improvements in walking balance.

**Trial registration:**

NCT01573585

**Electronic supplementary material:**

The online version of this article (doi:10.1186/s12883-014-0187-y) contains supplementary material, which is available to authorized users.

## Background

Balance ability is one of the most important factors in determining independence in daily activities and risk of falls following stroke [1]. Dynamic balance and mobility or ‘walking balance’ can be described as the ability to control the centre of mass (COM) within the base of support to remain upright during ambulation [2] and encompasses a range of walking-related tasks which challenge the balance system. The impact of diminished dynamic balance can be significant for stroke survivors. The resulting mobility limitations are associated with decreased self-efficacy, loss of independence, and restrictions in activities of daily living, community integration, and quality of life [3,4].

People following stroke struggle to produce sufficient power (the product of force and speed) with their paretic muscles; deficits in speed of movement are well-documented after stroke [5,6]. It has been suggested that power may be more important than absolute force production in functional mobility tasks, and velocity of movement may be instrumental to counteract potentially destabilizing forces exerted on an individual’s COM by gravity and environmental interactions (external perturbations) as well as voluntary movements (internal perturbations) [7,8]. Modest perturbations to quiet stance can be accommodated using an inverted pendulum model of balance control [9] in which the ankle musculature plays a pivotal role in the maintenance of stance, while activation of muscles around the hips is essential in responding to larger perturbations [10,11], particularly if a step is required to maintain balance - termed a stepping reaction [12]. There may be a greater reliance on stepping behaviours to avoid a fall after stroke than in healthy individuals [13]; however, impairments in paretic muscle activation make it difficult for these individuals to step with sufficient speed, coordination and amplitude to effectively to regain their balance [7,14,15].

Current clinical practice guidelines advocate task-oriented exercise programs involving the practice of ‘real life tasks’ following stroke [16], but specificity of task practice with respect to the speed required for postural reactions has received relatively little attention. A single session of fast functional squat and stepping training in stroke survivors has been found to improve paretic muscle activation and postural responses during an internal perturbation balance task after the exercises [15,17]. A recent case series reported improvements in walking balance that were retained for one year following a 12-session stepping retraining program in community-dwelling individuals with chronic stroke [18]. These changes in balance were accompanied by an increase in participation in meaningful activities in the community, and improvements in the movement kinematics of stepping reactions. These findings suggest that Fast muscle Activation and Stepping Training (FAST) may be an effective approach to improve walking balance following stroke.

The primary objective of this assessor-blinded, parallel design, randomized controlled trial is to investigate the effectiveness of an outpatient FAST program commenced within the first six months following stroke compared to an active control intervention of conventional outpatient physiotherapy (active control) that includes no targeted fast movement training for improving walking balance. As many people fall in the first few months after discharge from inpatient rehabilitation, this was thought to be an important window for this balance intervention [19]. The primary hypothesis is that improvements in walking balance (as measured with the Community Balance and Mobility Scale, CB&M [20,21]) will be larger following 12 sessions of FAST intervention compared to 12 sessions of active control intervention. The secondary hypothesis is that CB&M scores will continue to be higher in the FAST group compared to the active control group one month following the intervention. Another aim of this study is to explore potential mechanisms associated with improvements in walking balance including; improvements in walking speed, balance self-efficacy, ability to respond to internal and external perturbations to balance and associated changes in postural muscle activation. Our *mechanistic hypotheses* are that compared to the active control intervention; the FAST retraining will result in:Increased fast and self-selected natural walking speed (gait assessment);Reduced postural sway (balance perturbation assessment);Improved timing and amplitude of muscle activation (EMG onset timing, burst area and slope) during balance perturbations and gait;Increased balance self-efficacy (using Activities-specific Balance Confidence (ABC) scale).

## Methods

### Study design

The study is a single-blind, parallel design, randomized controlled trial, with the assessor blinded to the group allocation of the participants (Figure 1). The participants cannot be blinded to the interventions that they receive, though they will not be aware of the details of the other study arm. Eligible participants who provide written consent will be randomly assigned, to the FAST or active control group. Interventions will be received following discharge from inpatient rehabilitation in the outpatient departments of two hospitals in the Greater Vancouver area; Holy Family and Lion’s Gate Hospitals. Outcome measurements will be evaluated at the University of British Columbia at three time points (Figure 1): 1) baseline (prior to the first intervention session), 2) follow up (within one week of the 12th intervention session), 3) and retention (one month following the 12th intervention session) by the same blinded assessor. This study was approved by the University of British Columbia Human Research Ethics Committee. This protocol is reported in accordance with SPIRIT guidelines [22,23].

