### Group allocation and data management

Data will be managed using web-based software (EmPower Health Research, http://www.empowerhealthresearch.ca/). Upon registration, the software assigns each participant a unique identification number. Upon screening eligibility, providing signed consent and completion of the baseline assessment, participants will be randomized by the research coordinator using the integrated randomization software, “Integration”. This software protects allocation concealment by ensuring screening is complete and the participant is eligible prior to randomization as well as preventing multiple allocation of the same participant or unjustified removal of participants post-randomization. Participants will be stratified by their (combined leg and foot – affected limb only) CMSA score (≤8 or ≥9) to force a balance between groups in the motor recovery of the leg and foot. The randomization scheme is set up in permuted blocks of 2 and 4 to ensure a similar number of participants between groups and to prevent screening clinicians from guessing the next allocation. All outcome data will be entered into EmPower by the research coordinator, and the accuracy of data entry will be double-checked by a second person who will be blinded to participant group allocation. Research personnel who are to remain blind to group allocation (outcome assessors, data analysts) will not have access to the randomization form when they log into the database to enter data. The data management software contains an audit log that records the user with date and time stamps for all data entries, changes to data and explanations for changes. Data verification and the audit trail ensure high standards of data integrity and validity.

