### Intervention fidelity and monitoring of adverse events

Treatment physiotherapists who will be delivering the FAST and active control interventions will be provided with a treatment handbook outlining the intervention program. This material will be reviewed in a group training session with case examples and opportunities for discussion to provide feedback to refine and clarify the written materials. During the study, the research coordinator, an experienced physiotherapist and clinical researcher, will go to individual sites to facilitate the implementation of the proposed interventions, providing 1:1 guidance specific to the knowledge and beliefs of the treatment physiotherapists, their environment, and the needs of their participants while still ensuring the critical elements of the intervention are provided as planned [35]. Standardized recording forms (Additional files 1 and 2) developed with feedback from the treatment physiotherapists will be used to record the content and duration of interventions provided to the participants. The number of repetitions of activities, the level of assistance (overhead harness, transfer belt), scheduling of practice (blocked, semi-random, random) and feedback (immediate, summary) will be recorded for each FAST intervention session.

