#### Primary analysis

We will perform an analysis of covariance (ANCOVA), where the baseline CB&M score serves as the covariate; treatment group as the independent variable, and the follow up CB&M score as the dependent variable. To test our secondary hypothesis about retention, we will repeat this analysis with the retention CB&M score as the dependent variable.

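### Treating hospital is in neither the stratification nor the ANCOVA: a small, avoidable loss of precision, not a bias

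*Protocol article*

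**What the plan says.** All of this comes from the protocol article; no separate analysis plan is shown.

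- **Where treatment is given (Study design):** "Interventions will be received following discharge from inpatient rehabilitation in the outpatient departments of two hospitals in the Greater Vancouver area". The same section has every outcome measured at one university laboratory by one blinded assessor.
- **How delivery may vary (Intervention fidelity and monitoring of adverse events):** the research coordinator visits each site, "providing 1:1 guidance specific to the knowledge and beliefs of the treatment physiotherapists, their environment, and the needs of their participants". The sentence goes on to require that the core content be kept intact.
- **Randomisation (Group allocation and data management):** the only stratification factor is the combined leg and foot CMSA score, cut at 8/9, chosen "to force a balance between groups in the motor recovery of the leg and foot". On blocking: "The randomization scheme is set up in permuted blocks of 2 and 4".
- **Primary model (Primary analysis):** an ANCOVA "where the baseline CB&M score serves as the covariate; treatment group as the independent variable", with follow-up CB&M as the outcome. The retention analysis repeats it. Under Analyses of mechanistic outcomes, the other continuous outcomes are analysed in a similar way.

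Hospital appears in none of these. It is also absent from the participant characteristics listed for the exploratory regression.

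**The concern.** Both programmes are delivered one to one and tailored by the treating physiotherapist, and the protocol itself expects the local environment to matter. Screening and recruitment are also adapted to each site, so case mix may differ. Hospital is therefore a plausible predictor of follow-up CB&M beyond the baseline score, and it is known for every participant.

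With only 60 participants, two things follow from leaving it out. Any hospital difference widens the standard error of the group comparison. In an unlucky allocation, part of that difference is also carried into the estimated FAST effect. If hospital were added only after an imbalance had been seen, the adjustment would look data-driven.

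The protocol names both the stratification factor and the model terms. The point therefore concerns what the text fixes, not detail left to a document that is not shown.

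**Working it through.** **Inputs from the Sample size section:** 30 per group, effect size 0.60, baseline to follow-up correlation 0.75, CB&M SD 7.45, 5% type I error (taken as two-sided), 80% power. The effect of 0.60 is read in outcome SD, because the raw SD and the correlation are given separately.

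**Assumed, because the documents give no figure:** hospital shares of 30:30, with other splits shown; hospital effects of 0.3, 0.5 and 0.8 outcome SD.

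**1. The plan's own figure.** The ANCOVA formula gives n per group = 2(1.96 + 0.842)²(1 − 0.75²)/0.60² = 43.6 × 0.4375 = 19.1, so 20. The stated 30 is not reproduced at 80% power. It appears if 0.75 is squared twice (43.6 × (1 − 0.75⁴) = 29.8) or if the correlation is about 0.56. This is a separate point. It matters here only because 30 per group gives about 92% power in simulation on the stated inputs, which leaves a margin.

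**2. How large a chance imbalance can be.** With 30 of 60 allocated to FAST and 30 of 60 at one hospital, the SD of the between-arm difference in hospital share is √[0.5 × 0.5 × (2/30) × (60/59)] = 0.130, or 13 percentage points. From the hypergeometric distribution, the probability of a difference of 6 or more participants (20 points) is 19.6%. It is 17% at a 40:20 split and 7% at 45:15.

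**3. What a 20-point imbalance does.** Shift = 0.20 × hospital effect; in CB&M points, multiply by 7.45.

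| Hospital effect (SD) | Shift (SD) | CB&M points | Share of 0.60 |
|---|---|---|---|
| 0.3 | 0.06 | 0.45 | 10% |
| 0.5 | 0.10 | 0.75 | 17% |
| 0.8 | 0.16 | 1.19 | 27% |

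**4. What it does to the standard error.** With equal hospital shares, the error variance of the planned model is 1 − 0.75² + s²/4 for hospital effect s, and SE = √(variance × 2/30).

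- s = 0: √(0.4375/15) = 0.171
- s = 0.3: √(0.4600/15) = 0.175 (+3%)
- s = 0.5: √(0.5000/15) = 0.183 (+7%)
- s = 0.8: √(0.5975/15) = 0.200 (+17%)

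**5. Operating characteristics.** These come from simulation with 8,000 trials per scenario, about equal hospital shares, and no stratification by hospital.

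| s | Type I error, planned model | Power, planned model | Power, hospital term added |
|---|---|---|---|
| 0 | 5.3% | 92% | 92% |
| 0.3 | 4.8% | 91% | 92% |
| 0.5 | 4.8% | 89% | 92% |
| 0.8 | 4.7% | 83% | 93% |

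The mean error of the planned estimate was 0.003 SD or less in every scenario. Adding the term when hospital has no effect costs nothing visible.

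**6. Stratifying without adjusting.** When allocation was stratified by hospital but the model left hospital out, type I error fell to 2.6% and power was 87% at s = 0.8, against 92% with both. A stratification factor that predicts outcome belongs in the model. The same reasoning applies to CMSA, which is stratified on but absent from the ANCOVA.

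**The case against.** The strongest reply is that this is a refinement of precision and not a threat to validity. Participants are individually randomised, so hospital is independent of arm in expectation. The planned standard error already contains the hospital variance, and the simulation shows no bias and no excess of false positives. All of this stands.

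The reply can add that the protocol works to keep hospital differences small: a handbook, group training, recording forms, site visits with audit and feedback, a fixed number and length of sessions, common eligibility criteria, and one central blinded assessor. Baseline CB&M takes up part of any case-mix difference. This also stands, and it makes a hospital effect near 0.8 SD less likely. It does not show that the effect is zero.

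Two stronger readings are tempting and are not supported.

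- A reader might infer that site differences would pass for a FAST effect, so that the programme cannot be told apart from the place where it was given. That would require hospital to be tied to arm, and nothing in the protocol ties it.
- A reader might infer that each hospital has its own therapists. The text says only "Treatment physiotherapists who will be delivering the FAST and active control interventions will be provided with a treatment handbook". It does not say how therapists are divided between hospitals or arms.

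Finally, stratifying by hospital has a price. Physiotherapists at the two hospitals do the screening, and the blocks were chosen partly so that clinicians could not guess the next allocation. Separate lists per hospital with blocks of 2 and 4 would make the local sequence easier to predict. This objection holds, and it is why stratification is not the main recommendation.

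**Conclusion.** The point holds as a low-severity one. Treatment is given at two hospitals, and hospital enters neither the allocation nor the stated model. The cost is lost precision and, in about one allocation in five at an assumed even split, an imbalance of at least 20 points that would move the estimate by 0.06 to 0.16 SD or more for assumed hospital effects of 0.3 to 0.8 SD. The loss of power against a model with a hospital term is about 1, 3 and 10 percentage points at 0.3, 0.5 and 0.8 SD.

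The estimate is not biased and type I error is not inflated. Power stays above 80% across the whole range, although this rests on the stated correlation of 0.75; a weaker correlation would narrow the margin. The size of any hospital effect is assumed throughout.

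**What to change.** Before unblinding, prespecify treating hospital as a fixed effect, together with the CMSA stratum used in randomisation, in the CB&M ANCOVAs at follow up and at retention and in the parallel mechanistic ANCOVAs.

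The cost is one degree of freedom for hospital and one for CMSA stratum out of 60 participants. It needs no extra patients, visits or data, and the loss is negligible if hospital turns out not to matter.

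Stratifying by hospital is optional and open only if allocation has not begun. It would mean four lists (2 hospitals × 2 CMSA strata) in place of two, with more unfinished blocks and easier prediction of allocation in small local blocks. If it is adopted, the hospital term must also be in the model.

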**Figure 1 Fig1:**
[figure not shown]
**Design of the FAST Study.** Flow chart illustrating study design from initial contact with potential participants to retention assessment. CMSA, Chedoke-McMaster Stroke Assessment.

### Selection criteria and recruitment of participants

Individuals who have had their first stroke (confirmed by admission CT scan) within the previous 6-months that resulted in unilateral hemiparesis and required in-patient rehabilitation will be invited to participate if they also meet the following inclusion criteria:Sufficient motor control in the paretic lower limb to perform the stepping activities in the FAST program: Chedoke McMaster Stroke Assessment (CMSA) [24] leg and foot scored as stages 3–6 (stage 7 consider ‘normal’). CMSA leg and foot scores reflect the presence and severity of motor impairment following stroke, and they are used clinically to evaluate motor recovery [25].Standing balance ability necessary to participate safely in the FAST program: Berg Balance Score (BBS) ≥ 30/56 [26]. The BBS has established validity and excellent reliability in for assessing functional balance in people following stroke [27].Cognitive capacity to provide informed consent: Mini-Mental Status Examination score ≥ 24/30 [28].

We will exclude individuals with:Bilateral stroke or a history of previous stroke(s) for which inpatient rehabilitation was received.Severe co-morbidities likely to dominate the pattern of care (e.g. metastatic disease, severe congestive heart failure, etc.), co-existing peripheral neuropathies or vestibular disorders likely to independently have a negative impact on balance, and severe musculoskeletal problems or pain; as these conditions would be likely to impede participation in the study interventions.Global aphasia, receptive aphasia or language barriers who do not have someone to assist them in translating information, as these individuals would have difficulty providing informed consent or understanding exercise instructions.

The initial contact with potential participants will be made by the inpatient physiotherapist who is treating the potential participants at the two participating hospitals. The physiotherapist will ask them if they are interested in learning more about the study and, if interested, ask them if they will give consent to have the research coordinator review their chart to confirm eligibility. After reviewing their chart, the research coordinator will approach the prospective participant to describe the study in more detail or explain why they are not eligible. The research coordinator will review the letter of explanation and the consent form with the prospective participant and answer any questions. The research coordinator will return at least 24 hours later to obtain written consent before participating. Family members may be present to assist if there are any language barriers. All patients admitted with a primary diagnosis of stroke will be screened by their physiotherapists at two hospitals using a screening checklist. In accordance with CONSORT guidelines [29], the number of screened patients who are ineligible (and the reasons for ineligibility) or who are potentially eligible but are not interested in the study will be recorded.

To optimize recruitment, all members of the stroke rehabilitation teams at each recruitment site including physiotherapy managers, site coordinators, intake clerks and physiotherapists will be engaged in refining the processes for screening and recruitment specific to their organizations; strategies that are tailored to the sites will be developed collaboratively including reminders, flow charts for processes and communication, and screening forms designed to minimize burden for the site staff and their patients. These processes will be reviewed and revised based on feedback and will be sustained by onsite coordinators who serve as local leaders and champions for the study in collaboration with the research coordinator.

